#### 8.1.2 Secondary study parameters/endpoints

Secondary outcome parameters are adverse events/toxicity, cumulative cisplatin dose, time to recurrence, 2-year overall survival, costs, quality of life and patient's preference. The main oncological outcome parameters are time to recurrence and survival. Clinically relevant treatment related toxicity parameters, including specific toxicity that results in significant (grade 3 or 4) toxicity, treatment de-escalation or termination, will be recorded by the treating medical oncologist. Toxicity will be scored according to the Common Terminology Criteria for Adverse Events (CTCAE) guidelines, v5.0.

#### Quality of life questionnaires

The following questionnaires will be used to measure quality of life: EORTC QLQ-C30, EORTC-QLQH& N35 and EQ-5D-5L. Global quality of life is assessed with the EORTC-QLQ-C30 global measure. The EORTC-QLQ-H&N35 is designed to be head and neck cancer-specific, multidimensional in structure, appropriate for self-administration and applicable across a range of cultural settings. The EQ-5D-5L is a standardized instrument can be used as a quantitative measure of health outcome that can be used in a wide range of health conditions and treatments, and reflects the patient's own judgement.

Questionnaires are asked to fill out before and 3, 6, 12 and 24 months after CRT. Standard scoring methods are applied to quality-of-life questionnaires. All scores are normalized, ranging from 0 to 100, and transformed to unweighted summated scales in which higher scores indicates better health. Separate comparisons are made at each time point.

Unadjusted p values are used. On the EORTC questionnaires a 10-point difference in scores was considered to be clinically relevant.

#### Cost analysis

Substitution of weekly low dose cisplatin for three-weekly high dose cisplatin in patients treated with concurrent CRT is expected to result in cost-savings and an increase in quality of life due to reducing the number of complications. A detailed analyses of cost differences for low SMM patients with weekly low dose cisplatin and standard of care (three-weekly high dose cisplatin) demands a detailed collection of all health care consumed by these patients in relation to the intervention and complications. In the prospective cohort we will collect all

health care consumed by patients in each of the three different groups with a follow-up of 12 months. All data will be collected from the electronic patient files in each different hospital and will be collected using respective units for each sort of health care consumption (hospital stay per day, cost per dose, etc.). As indicated, quality of life will be measured before and 3, 6, 12 and 24 months after CRT using the EQ-5D-5L. Productivity loss of low SMM patients will be collected during the study at baseline and at 12 months after CRT using the productivity cost questionnaire (PCQ). This will only be done for the low SMM group, since our main interest is the difference between the two chemotherapy schemes in the low SMM group. All different units of care consumed will be linked to their respective unit costs. Reimbursement prices issued by the Dutch Healthcare Authority (NZA) and national reference prices will be used for this assessment as outlined in current Dutch pharmacoeconomic guidance.

In addition to total health care consumption of these patients it is essential to perform micro-costing of CRT treatment to have detailed insight in the additional costs. We therefore aim to perform a micro-costing study using the activity based costing (ABC) method. To link both costs and effects we aim to develop a decision-tree completely outlining all probabilities of having complications (CDLT resulting in non-compliance) and their respective costs and effects (quality of life) in each of the three different groups. Outcome measure will be incremental costs per quality adjusted life year. Moreover, complete sensitivity analysis (both deterministic as well as probabilistic) will be carried out to have detailed insights into the impact of uncertainty on our outcome measures. In addition to a cost-effectiveness analyses we aim to perform a budget impact analysis (BIA) as well. The BIA adheres to the Zorginstituut guidelines and applies the perspectives: societal, health insurance/third party payer and health care (Budgetair Kader Zorg (BKZ)). The BIA Prices will be linked to perspectives: societal-CEA based prices, BKZ-average rates according to NZa, for health insurance perspective also NZa average rates and, for example, for a local health care provider perspective specific passenger rates ('passanten tarieven'). The BIA will be assessed through (decision analytical) modelling and analyzed in a probabilistic way.

### **8.1.3 Other study parameters (if applicable)**

To allow for comparison with the recent nation-wide Dutch Head and Neck Society audit, the same characteristics and potential predictive factors will be scored.

Collected patient characteristics are gender, age, weight, stature (length), smoking history, use of alcohol, loss of weight, Eastern Cooperative Oncology Group (ECOG performance status), medical history regarding heart, lung, diabetes mellitus, oncology and nephrology, grip strength (if available), comorbidity (ACE-27 and Charlson Comorbidity Index), Tumor Node Metastasis (TNM) classification, tumor localisation, estimated Glomerular Filtration Rate (eGFR), serum creatinine, neutrophil count, platelet count, leukocyte count, lymphocyte count, monocyte count and hemoglobin level, baseline audiometry results and treatment plan (including use of co-medication).

## 8.2 Randomisation, blinding and treatment allocation

When the patient has signed informed consent, patients with low SMM will be randomised by the investigator for three-weekly high dose (three cycles 100mg/m^2) or weekly low dose cisplatin (seven cycles 40mg/m^2). Allocation is performed by a central office on-site computer combined with allocations kept in a locked, unreadable computer file that investigators can assess only after the characteristics of an enrolled patient are entered. A stratified permuted-block procedure will randomise patients to the groups on a 1:1 ratio. Strata comprises center and two groups according to AJCC staging:

- 1) Stage I-III
- 2) Stage IV.

Neither patients, investigators nor office personnel are blinded to the group chosen by the allocation procedure.

## 8.3 Study procedures

All patients diagnosed with an indication for primary CRT, will be identified and screened for eligibility at a weekly multidisciplinary head and neck oncology meeting. SMM will be measured on routinely performed pre-treatment (PET-)CT or MRI of the head and neck. During the multidisciplinary meeting, it will be decided whether the patient has an indication for primary CRT. If the patient is considered for cisplatin CRT, the investigator will inform the patient about the study and asked to sign informed consent. Patients with normal or high SMM (>43.2 cm^2/m^2) will receive the standard cisplatin scheme, which differs per centre. This will either be three-weekly high-dose cisplatin of 100 mg/m^2 or a weekly low-dose cisplatin of 40 mg/m^2. Patients with a low SMM ≤43.2 cm^2/m^2 will be randomised for either low- or high-dose cisplatin, respectively 40 mg/m^2 or 100 mg/m^2. Dependent on each centre, the local pharmacy or the local pharmacy and study pharmacy will be involved since treatment with cisplatin is standard of care and the planned cumulative dosage for both groups will be comparable.

The 100 and 40 mg/m^2 schemes differ in dose and frequency, but also in administration: three times hospital admission versus 7 day visits at the (outpatient) clinic. Because every patient receives radiotherapy daily (which is part of the standard of care), no additional hospital visits are required. In case of CDLT, the treating physician will decide which therapy is most suitable to the patient. It is conform standard guidelines to switch to different type of therapy when cisplatin has become too toxic. There will be no cross-over from the high to low-dose group, since this is against standard of care in which cisplatin therapy is stopped and carboplatin is given instead. The data will still be eligible for analysis in this research. During treatment, the patient will frequently be seen by the treating radiotherapist and oncologist. Adverse events, such as toxicities and CDLT are reported in the EPR according to standard hospital guidelines. Two to three days after each cisplatin dose, the kidney function will be determined. The investigator will collect clinical relevant data for each week of treatment. Data collected include CDLT, cause and type of acute toxicity, grade of toxicity according to Common

Terminology Criteria for Adverse Events (CTCAE) v5.0 guidelines (CTCAE), treatment to reduce toxicity and/or side effects and change of treatment strategy (e.g. switch from cisplatin to carboplatin). During follow-up, the patient is seen by the treating physician according to a standardized scheme. The investigator will collect data at 3, 6, 12 and 24 months after end of CRT, with a possible delay of maximum 6 weeks. Data consist of early and late toxicities, recurrence, residual disease, lost-to-follow-up and death.

Relevant and related early and late toxicities during and after CRT will be classified according to CTCAE v5.0 criteria with additional datacollection for toxicities concerning renal function, bone marrow dysfunctioning, hearing loss and neurotoxicity. Other adverse events not specified by CTCAE v5.0 will be described by the investigator in terms of symptoms, severeness, treatment and outcome. For each toxicity/event, date of start symptoms, date of diagnosis, treatment type, date of start and date of end of treatment will be collected. It will be stated whether the symptoms resolved, remained or improved and when this happened.

**Nephrotoxicity:** In case nephrotoxicity occurs, the eGFR, creatinine, and if available magnesium before CRT, during kidney dysfunction and at last moment of follow-up will be collected and compared as well.

**Ototoxicity:** When the treating physician suspects hearing loss in a patient, additional audiologic exam three months after CRT is recommended according to standard practice. Audiometry results and symptoms such as otitis, hearing loss and tinnitus, will be collected in the database to assess possible ototoxicity. Grading will be done using CTCAE v5.0 and the local preferred grading system.

**Neurotoxicity:** Neurologic symptoms will be assessed as either peripheral motor or sensory neuropathy. Other neurologic symptoms, possible related to HNSCC treatment, not classified as peripheral neuropathy will be described.

**Bone marrow dysfunctioning:** To assess degree of bone marrow dysfunctioning, blood cell count will be collected in the database. Grading will be done according to several CTCAE v5.0 subcategories 'White blood cell decreased', 'Neutrophil count decreased', 'Anemia' and 'low platelets'.

Extra procedures for this study are limited to questionnaires:

- Questionnaire EORTC QLQ-C305
- Questionnaire EORTC-QLQ-H&N3
- Questionnaire EQ-5D-5L
- Questionnaire Productivity Cost Analysis (PCQ) for low SMM patients only
- Semi structured interview 3 months after treatment

*Skeletal muscle mass measurement*

SMM will be measured on pre-treatment standard CT, MRI or PET CT, made during routine diagnostic work-up.

Cross-sectional muscle area (CSMA) is usually measured on a transversal single slice of the third lumbar vertebra (L3) leading to a lumbar skeletal muscle index (lumbar SMI) when corrected for stature. This SMI correlates with total skeletal muscle volume measured on whole-body magnetic resonance imaging (MRI).

In head- and neck cancer patients, head and neck CT-scan instead of an abdominal CT-scan is routinely performed. However, by measuring the CSMA of the sternocleidomastoid muscles (SCM) and paravertebral muscles (PVM) on a transversal single slice of the third cervical vertebra (C3), SMM can be easily and reliably assessed.

Muscle tissue was identified using Hounsfield Unit (HU) range settings from -29 to +150 HU, which is specific for muscle tissue. Muscle tissue was delineated at the level of the third cervical vertebra (C3). The SMA was defined as the pixel area within the delineated area with a radiodensity between -29 and +150 HU. Delineation of muscle tissue was manually performed using the Slice-O-matic software v 5.0 (Tomovision, Canada). Muscle tissue delineation at the level of C3 was performed by selecting the first slide showing both transverse processes and the entire vertebral arc when scrolling from caudal to cranial direction. The contours of the paravertebral muscles and both sternocleidomastoid muscles were manually traced. The SMA at the level of C3 was calculated as the sum of the paravertebral muscle and both sternocleidomastoid muscles. If evident lymph node metastasis hindered accurate delineation of one sternocleidomastoid muscle, the SMA of the contralateral sternocleidomastoid muscle was used as an estimation of the SMA of the affected sternocleidomastoid muscle. After delineation, SMA was automatically retrieved from Slice-O-matic (v5.0, TomoVision, Montreal, Canada). For MRI, muscle area was manually segmented, and fatty tissue was manually excluded. The overall intraclass correlation coefficient (ICC) for the muscle SMA obtained by CT and MRI has shown to be excellent (ICC 0.9,  $p < 0.01$ ), and can therefore be used interchangeably for measuring CSA at the level of C3. The cervical SMI (CSMI) was calculated by dividing the SMA at the level of C3 by the squared height of the patient.

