### 10.2 Secondary study parameter(s)

Treatment toxicity is assessed with the Common Toxicity Criteria Adverse Events (CTCAE) v5.0 for a period of 24 months from the end of treatment. Toxicity scored as CDLT by the treating physician will be assessed, clarified if necessary, and reconfirmed separately. A severe toxic event is defined as a toxicity assessed as grade 3–5. Toxicities are classified as acute if they first appeared during or up to 3 months after treatment, and are classified as late if they persist, or first appear, more than 3 months after treatment. Multiple occurrences of events of a single toxicity type within an analysis time period are counted as a single event. Median numbers of toxicity events per patient (short-term [acute] toxicity and adverse long-term [late] effects, based on the TAME method of reporting toxicities) are compared between trial arms using t-tests. Proportions of patients affected by one or more toxicity event are compared between trial arms using Fishers exact test. Total administered cisplatin dose will also be recorded and means (or medians depending on the distribution) compared between trial arms.

Overall survival, disease-specific survival, loco-regional recurrences and time to recurrence are measured from the starting date of chemotherapy and compared between the three groups by the log-rank test with all-cause mortality in the intention-to treat population. Deaths are classified as being due to head and neck cancer or to other causes. Recurrences can be loco-regional or distant, or both. Patients who died from head and neck cancer causes as the first event are classed as recurrences. Patients on follow-up and patients lost to follow-up are censored at the last date at which they were known to be alive. Total time of follow-up per patient is two years. Hazard ratios and 95% CIs are generated with a univariate Cox proportional hazards model. The Schoenfeld residuals are tested by plotting the observed Kaplan- Meier values against the Cox predicted values. The effect of randomised treatment on outcome is also assessed after adjusting for known prognostic factors with a multivariate Cox proportional hazards model. At 3 months after treatment semi-structured interviews are conducted to obtain a better understanding of the patients' experience and preference for the treatment schemes, until saturation is reached. Semi-

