### **11.4 Benefits and risks assessment, group relatedness**

It is expected that patients with low skeletal muscle mass, might benefit from a low-dose weekly cisplatin regimen in terms of increased compliance and cumulative received cisplatin dose, less adverse events and improved quality of life. We think that the 40 mg/m^2 arm will show comparable side effects to the 100 mg/m^2 arm, however the hypothesis is that the frequency and extent of these side effects will decrease. Only questionnaires, which will take a small amount of time, will be the extra burden on both the intervention and control arm. No other diagnostics will be performed in comparison to standard treatment. We consider both schemes as clinical equipoise

according to expert opinion. In both schemes we aim to give a cumulative dose of more than 200 mg/m^2 and both schemes are used in daily clinical practice.

For the HNSCC patient group with low skeletal muscle mass, this study may serve as a basis for a personalized cisplatin dosing regimen in the future. This might result in less severe treatment related toxicity, less treatment de-escalation or termination, and possibly also a higher disease specific survival.

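### Post-treatment audiometry depends on the suspicion of an unblinded physician, so detection of hearing loss can differ by arm in the toxicity comparison

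*Protocol*

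**What the plan says.** - **Trigger for testing.** Protocol 8.3 (Ototoxicity): "When the treating physician suspects hearing loss in a patient, additional audiologic exam three months after CRT is recommended according to standard practice". The test is recommended, not required.
- **Use of the result.** The same paragraph continues: "Audiometry results and symptoms such as otitis, hearing loss and tinnitus, will be collected in the database to assess possible ototoxicity". Audiograms and symptoms therefore both contribute.
- **Grading.** "Grading will be done using CTCAE v5.0 and the local preferred grading system" (8.3).
- **Baseline.** Section 8.1.3 lists "baseline audiometry results and treatment plan (including use of co-medication") among the data collected.
- **No scheduled follow-up test.** "Extra procedures for this study are limited to questionnaires" (8.3, where the list also includes an interview), and "No other diagnostics will be performed in comparison to standard treatment" (11.4).
- **Blinding.** "Neither patients, investigators nor office personnel are blinded to the group chosen by the allocation procedure" (8.2).
- **Analysis.** Toxicity is a secondary outcome (8.1.2). In 10.2 the number of toxicity events per patient is compared between arms, and "Proportions of patients affected by one or more toxicity event are compared between trial arms using Fishers exact test". Repeated events of one toxicity type within an analysis period count once.

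**The concern.** An audiometric finding can enter the record only if someone orders the audiogram. Here the person who decides knows the schedule the patient received, and section 11.4 hypothesises that side effects will be less frequent and less extensive on the weekly schedule. If the threshold for suspicion differs by arm, recorded hearing loss can differ even when true hearing loss does not.

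The protocol treats kidney function differently: section 8.3 has it determined two to three days after each cisplatin dose, with no need for suspicion.

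Sections 1 and 6.3 name ototoxicity among the late adverse events that compromise quality of life. Fewer side effects is part of the case for weekly dosing, so readers will look at this component. Without the number tested in each arm, they could not separate a true difference from a difference in testing. An analysis plan written later cannot recover hearing data that the procedures in 8.3 never obtained.

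**Working it through.** **Plan's own figures.** The protocol gives no rate, target or power for ototoxicity. The only figure needed is the number randomised. Section 4.4 states 33 per arm for compliance of 55.7% against 86.3% (two-sided 0.05, power 80%). The pooled normal approximation gives 34 per arm, and 33 per arm gives 79.6% power, so the stated figure reproduces closely. With 5% drop-out, 66 / 0.95 = 69.5, rounded up to 70, or 35 per arm.

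**Model.** Let *t* be the true rate of hearing loss, the same in both arms, and *d*₁ and *d*₂ the probabilities that a true case is detected in each arm. All three are assumptions.

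- Recorded rate in arm *i* = *t* × *dᵢ*
- Expected spurious difference = *t* × (*d*₁ − *d*₂)

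For example, 0.30 × 0.80 = 0.24 and 0.30 × 0.50 = 0.15, a difference of 9 points.

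The last column is the exact probability that a two-sided Fisher test on hearing loss alone gives p < 0.05 with 35 per arm, found by enumerating both binomial distributions.

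| True rate | Detection | Recorded | Difference | Fisher p < 0.05 |
|---|---|---|---|---|
| 30% | 100% / 100% | 30% / 30% | 0 | 2.8% |
| 30% | 70% / 70% | 21% / 21% | 0 | 2.5% |
| 30% | 80% / 60% | 24% / 18% | 6 | 5.4% |
| 30% | 80% / 50% | 24% / 15% | 9 | 9.7% |
| 30% | 90% / 50% | 27% / 15% | 12 | 15.6% |
| 40% | 90% / 50% | 36% / 20% | 16 | 23.5% |
| 50% | 90% / 50% | 45% / 25% | 20 | 33.8% |

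Equal but incomplete detection produces no difference between arms. It only lowers both rates.

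**What reaches section 10.2.** That section names no ototoxicity-only test, so the table shows the component and not a planned analysis.

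- *Events per patient.* If hearing loss counts as one event type, the mean count shifts by the full difference, for example 0.09 events per patient in the 9-point case.
- *Proportion with one or more events.* Hearing loss changes a patient's status only if that patient has no other event. If a fraction *q* has no other event, equal in both arms and independent of hearing loss, the shift is *q* × *t* × (*d*₁ − *d*₂). The protocol gives no *q*. As a rough range, the toxicity rates it cites from a randomised adjuvant trial (84.6% and 71.6%) give *q* = 1 − 0.846 = 0.154 and 1 − 0.716 = 0.284. The 9-point case then becomes 9 × 0.154 = 1.4 to 9 × 0.284 = 2.6 points. The 16-point case becomes 2.5 to 4.5 points.

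The model treats detection as one probability. Recording symptoms without an audiogram raises *d* in both arms, and may narrow the gap or leave it.

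**The case against.** The strongest reply is that this is a deliberate and disclosed choice. The trial is low-intervention, adds no diagnostics, and leaves audiometry to standard practice. Symptoms are collected as well, so an untested patient with hearing loss can still be recorded. The component is small within 10.2, and the primary outcome does not use the three-month audiogram. All of this stands. It explains why audiograms are not mandated and it limits the consequence. It does not make suspicion-driven results comparable between arms, and the protocol does not say that every patient is asked about hearing.

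Three stronger readings are tempting, and the protocol supports none of them:

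- **Untested patients are counted as free of hearing loss.** The protocol does not say how a missing audiogram is coded. Symptoms are a second route to an event, and section 10 allows multiple imputation if needed.
- **Local grading spoils the comparison.** The local scale is additional to CTCAE v5.0, and 10.2 assesses toxicity by CTCAE v5.0. Nothing says that local grades are pooled.
- **The bias favours weekly dosing.** Section 11.4 makes that direction plausible, but the same section calls the schedules clinical equipoise, and section 13.2 says the hypotheses could equally hold for the three-weekly dose. Bias between arms also requires detection to differ by arm, which cannot be established in advance.

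**Conclusion.** The concern holds in a limited form. Followed exactly, the plan allows detection of audiometric hearing loss to differ by arm, and those findings feed the toxicity comparison in 10.2. A difference in that component could therefore reflect testing and not toxicity.

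Size and direction cannot be derived from the protocol. Under the assumed rates, the spurious difference in hearing loss alone runs from 0 with equal detection to 20 points with a large imbalance. The shift in the proportion with any toxicity would be a fraction of that. Even in the 9-point case, more than 90% of trials of this size would show no significant difference in hearing loss.

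This affects one component of a secondary endpoint. The primary compliance comparison is not touched. The change is worth making because it is cheap and because hearing information not collected uniformly cannot be recovered later.

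**What to change.** 1. **Section 8.3.** State that hearing loss and tinnitus are asked of every randomised patient and scored by CTCAE v5.0 at the existing 3, 6, 12 and 24 month collection points, whether or not the physician suspects a problem.
2. **Section 10.2.** State that the between-arm ototoxicity comparison rests on these uniformly collected data.
3. **Audiometry.** Report results descriptively, with the number tested in each arm.
4. **Sensitivity analysis.** Repeat the toxicity counts with and without events found only by suspicion-driven audiograms.

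The cost is wording in two sections and one line on the follow-up form. No audiometry is added, so the statements in 8.3 and 11.4 that no extra diagnostics are performed can stay.

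There are two small downsides. Symptom reports come from unblinded patients to unblinded staff, so the bias is reduced and not removed. Subclinical hearing loss is not compared between arms. Scheduled audiometry for all, graded by an assessor unaware of the arm, would go further but would require those statements to be revised.

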### 3. STUDY DESIGN

In this multicenter prospective randomised low intervention clinical trial, the compliance of weekly low dose cisplatin with concurrent radiotherapy in LA-HNSCC patients with low SMM will be investigated. SMM will be measured on routinely performed (PET-)CT or MRI scans before the multidisciplinary head and neck cancer meeting by the treating physician. Patients who are found eligible by the multidisciplinary team and are planned for cisplatin based concurrent CRT will be asked to participate in this study by the investigator. Seventy patients with low SMM will be randomised between weekly low dose and three-weekly high dose cisplatin. To assure the inclusion of seventy patients with low SMM, 129 patients in total are needed as explained in paragraph 4.4. Therefore 59 patients with normal skeletal muscle mass will be asked to participate as well. They will receive the most standard cisplatin scheme for the centre they are admitted to specifically and will be included in follow-up. Baseline characteristics and outcomes will be collected for all patients.

SMM will be estimated using a validated technique based on measurement of the cross-sectional area of the sternocleidomastoid muscle and paravertebral muscles on the level of C3 on routinely performed CT or MRI. In patients who underwent fluorodeoxyglucose-positron emission tomography(FDG-PET)/CT as part of the diagnostic work-up, as a control of SMM measurement at the level of C3, SMM will also be measured at the level of L3, which is the most commonly used method in medical literature as a control of SMM measurement at the level of C3.

Based on the cut-off value calculated by Wendrich et al., low SMM is defined as skeletal muscle mass  $\leq 43,3 \text{ cm}^2/\text{m}^2$ . Patients with low SMM will be randomised between weekly low dose cisplatin and three-weekly high dose cisplatin with concurrent RT. The rate of compliance to proposed cisplatin scheme will be compared between three groups: patients with low SMM with weekly low dose cisplatin, patients with low SMM and three-weekly high dose cisplatin and the rest group of normal SMM receiving the local standard scheme, which is three-weekly 100 mg/m^2 cisplatin in the UMC Utrecht, Noordwest Ziekenhuisgroep, Leiden University Medical Center, and VUmc, and weekly 40 mg/m^2 cisplatin in the NKI-AVL.

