### 4.3 Exclusion criteria

A potential subject who meets any of the following criteria will be excluded from participation in this study:

- mentally disabled or patients with significantly altered mental status that would prohibit understanding and giving informed consent;
- a history of bilateral lymph node dissection in the neck and no available (PET-)CT scan of the third lumbar vertebra;
- an absolute contraindication for cisplatin as defined by the treating physician, including relevant pre-existing kidney insufficiency, clinically apparent vascular disease (for example

claudicatio intermittens), clinically relevant perceptible deafness, serious neuropathy and poor performance score;

- an absolute contraindication for high dose three-weekly cisplatin 100 mg/m^2 as defined by the treating physician;
- interval between diagnostic scan and planned CRT >2 months;
- cisplatin CRT planned as non-primary or induction treatment.

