#### 4.4 Sample size calculation

In the retrospective study by Wendrich et al., out of 112 patients 30.4% experienced CDLT (meaning compliance to chemotherapy regimen was 69.6%). Using a cut-off 43.2 cm^2/m^2, 54.5% patients had low SMM. Patients with low SMM experienced CDLT more frequently than patients with normal SMM (44.3% vs. 13.7%,  $p < 0.001$ ). Thus compliance rates to chemotherapy regimen were 55.7% and 86.3%, respectively. We hypothesize therefore that in patients with low skeletal muscle mass and weekly low dose cisplatin, also 86.3% compliance will be reached. If we compare this compliance to an expected compliance of 55.7% in the arm of with a three-weekly high dose cisplatin, 33 patients with low SMM per arm are needed to show that the compliance in the weekly low dose cisplatin scheme is statistically significantly better than the threeweekly high dose scheme (two-sided alpha 0.05 and power 80%). With an expected drop-out of 5% 70 patients with low SMM are needed. Power calculations were done using PASS software. Since 54.5% of patients undergoing cisplatin based concurrent CRT have low SMM, to find the 70 patients with low SMM a total of 129 LA-HNSCC patients undergoing cisplatin based concurrent CRT are needed.

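### The muscle index that decides randomisation is not tied to its cut-off: the only written formula is on a scale that does not fit 43.2 cm²/m², and the cut-off itself appears with two values

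*Protocol*

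**What the plan says.** The randomisation rule is in section 8.3: "Patients with a low SMM ≤43.2 cm 2 /m 2 will be randomised for either low- or high-dose cisplatin". Patients above 43.2 form the normal-SMM group and receive their centre's standard scheme.

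The measurement is described later in the same section. The area is defined first: "The SMA at the level of C3 was calculated as the sum of the paravertebral muscle and both sternocleidomastoid muscles". The index follows: "The cervical SMI (CSMI) was calculated by dividing the SMA at the level of C3 by the squared height of the patient". The description ends there. A lumbar index is mentioned only as background, as the usual L3 measurement "leading to a lumbar skeletal muscle index (lumbar SMI) when corrected for stature".

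Section 4.4 takes the prevalence from a retrospective study: "Using a cut-off 43.2 cm 2 /m 2 , 54.5% patients had low SMM". It derives the recruitment total of 129 from that share, and the planning rates from the same two groups: "Thus compliance rates to chemotherapy regimen were 55.7% and 86.3%, respectively".

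Sections 3 and 4.1 use L3 as a check on the C3 value. Section 4.3 goes further. It excludes patients with "a history of bilateral lymph node dissection in the neck and no available (PET-)CT scan of the third lumbar vertebra", so a patient with bilateral dissection who does have an L3 scan stays eligible and would have to be classified from it.

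Section 3 sets low SMM at 43.3 cm²/m² or below, crediting the same retrospective study that section 4.4 cites for 43.2.

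**The concern.** One number decides whether a patient is randomised or joins the non-randomised comparison group. A person doing the measurement needs three things from the protocol: which area to measure, how to turn it into the index, and the cut-off on that index. The protocol gives an area and an index at C3, and a cut-off, but never says that they belong together. Taken together, they give a result that contradicts the protocol's own prevalence.

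The normal-SMM group is needed for the first secondary objective (section 2) and the three-group comparison (section 3). The 55.7% control rate in section 4.4 belongs to patients who were low on the source study's index. If a centre worked from the printed formula, patients meant for the comparison group would be randomised, and the randomised population would no longer be the one behind 55.7%. Section 3 places the measurement with the treating physician, so the written rule has to stand on its own.

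**Working it through.** **1. The plan's own figures.** Inputs from section 4.4: 55.7% v 86.3%, two-sided alpha 0.05, power 80%, drop-out 5%, 54.5% low SMM.

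- Per arm, pooled normal approximation: [1.96·√(2·0.71·0.29) + 0.8416·√(0.557·0.443 + 0.863·0.137)]² / 0.306² = 33.3, so 34. Power at the stated 33 is 79.6%, so 33 is reproduced within rounding.
- Drop-out: 66/0.95 = 69.5, so 70.
- Recruitment: 70/0.545 = 128.4, so 129, leaving 129 − 70 = 59 normal.

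The totals of 129 and 59 therefore require about 45.5% of patients to lie above the cut-off.

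**2. Muscle area that the written index needs to reach 43.2.** Area = 43.2 × height².

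- 1.60 m: 110.6 cm²
- 1.70 m: 124.8 cm²
- 1.75 m: 132.3 cm²
- 1.80 m: 140.0 cm²

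**3. Comparison with the whole neck.** The documents give no neck sizes or C3 areas. I assume a circular neck of circumference 34 to 42 cm, with area = circumference²/(4π). The table shows the share of the entire cross-section that the two muscle groups would have to fill.

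| Height | 34 cm (92.0 cm²) | 38 cm (114.9 cm²) | 40 cm (127.3 cm²) | 42 cm (140.4 cm²) |
|---|---|---|---|---|
| 1.60 m | 120% | 96% | 87% | 79% |
| 1.70 m | 136% | 109% | 98% | 89% |
| 1.75 m | 144% | 115% | 104% | 94% |
| 1.80 m | 152% | 122% | 110% | 99.7% |

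Even the most favourable cell needs 79% of a section that also holds vertebra, airway, fat and other tissue. As a second check, assumed C3 muscle areas of 20 to 80 cm² at heights of 1.55 to 1.85 m give indices from 20/1.85² = 5.8 to 80/1.55² = 33.3, all below 43.2.

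**4. Effect on the 70/59 split if the formula were followed literally.** If a share f is classed low, 70 low-SMM patients are reached after 70/f recruits.

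- f = 54.5%: 129 recruits, 59 normal (the plan)
- f = 90%: 78 recruits, 8 normal
- f = 95%: 74 recruits, 4 normal
- f = 100%: 70 recruits, 0 normal

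As an illustration of the limit, suppose everyone were randomised. The control rate would then be the overall 69.6% in section 4.4. With 86.3% kept in the weekly arm, power at 33 per arm would be 37%, and 80% power would need 96 per arm.

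**5. 43.2 against 43.3.** Assume a normal distribution with SD 5 to 11 cm²/m² and 54.5% at or below 43.2. The share between the two values is then 0.8% down to 0.4%, or 1.0 down to 0.5 of 129 patients.

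**The case against.** The strongest reply is that the protocol never says the cut-off applies to the cervical index. Sections 3, 4.4 and 8.3 attach it to low SMM. Sections 1 and 3 speak of SMM being estimated from the C3 area by a validated method, with citations. A further step may well be intended, and may be used in practice. This stands, and it limits the point to a missing link and a scale that does not fit. It does not remove the point, because no section supplies the step.

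The geometry rests on assumed sizes, and the assumed whole-neck range overlaps the required areas: at 1.60 m, a 38 cm neck (114.9 cm²) exceeds 110.6 cm². This also stands. The argument needs the added fact that these muscles are only part of the neck, so no exact percentage classed low can be derived from the documents.

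A centre finding no normal-SMM patients would probably notice, given that 59 are planned. That is fair, and it makes silent failure across the whole trial unlikely. The use of L3 as a replacement is confined to a small group, and the 43.2/43.3 conflict is numerically trivial.

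A reader might infer three stronger things that the documents do not support:

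- **That patients have been misclassified.** Nothing shows how the index was calculated in practice.
- **That close to 100% would be low as a matter of fact.** This depends on assumed neck sizes and muscle shares.
- **That the source study converted C3 area to an L3 value by an equation left out here.** The documents state no such conversion, so it can only be put to the sponsor as a question.

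**Conclusion.** The point holds as a defect in the written definition of the randomisation variable. The only index formula is C3 muscle area over height squared, and no step connects it to 43.2 cm²/m². On that raw scale the cut-off needs 111 to 140 cm² of two neck muscle groups at 1.60 to 1.80 m, which is incompatible with 54.5% low SMM and with 70 low and 59 normal patients. Read literally, the formula would class most or nearly all patients as low. That inference rests on the assumed circumferences of 34 to 42 cm and on muscle filling only part of the neck.

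The missing rule for a directly measured L3 value is part of the same gap. The 43.2/43.3 conflict is genuine but minor, at about one patient in 129 at most under the assumed SD. It would not carry the point alone. The index problem does, because it governs who is randomised and is cheap to settle.

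**What to change.** - In section 8.3, state the full calculation from the measured C3 area to the index on which the cut-off was derived, including any conversion, with the sponsor confirming it against the source study. Alternatively, give a cut-off on the C3 scale. Say explicitly that the cut-off applies to that index.
- State how a directly measured L3 value is used for classification, at least for the patients whom section 4.3 keeps eligible on the strength of an L3 scan.
- Reconcile section 3 with sections 4.4 and 8.3 to one cut-off verified against the source. At present the 54.5% and the randomisation rule rest on 43.2.
- Check that patients already enrolled were classified by that calculation and cut-off.

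The cost is a few sentences in an amendment and one check of existing classifications. If the check confirms that the intended calculation was used throughout, the sample size needs no change on this account.
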